### Study design

2.6.

Figure 1 shows the flow chart of this study. Participants will take ubiquinol orally with a dose of 200 mg daily or a placebo for 14 days before departure. Physical examination, symptoms related to high-altitude acclimatization and de-acclimatization, cardiorespiratory exercise test, laboratory test, and any possible adverse reaction of ubiquinol and exercise will be collected at baseline detection and each visit. During the 14 days of the medication, only participants who did not experience these adverse effects would go to the high altitude as scheduled. It would help us identify related symptoms at high altitudes due to hypoxia rather than adverse events of ubiquinol. The laboratory and exercise tests will be conducted separately on the last three days of the 14 days. Subsequently, they will board a flight to Shigatse (high altitude area, 3,900 m) in 3 h. After arriving at Shigatse, the AMS symptom self-administered questionnaires and adverse reactions of ubiquinol will be followed up daily, and the other prior programs will be carried out on the third day. The subjects will then be flown back to a low altitude after staying for 7 days at a high altitude and scored for HADAS, followed by other prior programs at a low altitude on the 7th day after return. The last visit will be set in the sixth month of this study, which has not yet been conducted. Laboratory tests include a blood routine test of 19 parameters commonly used in the clinic and a serological test of 19 circulating indicators, including glucose, total cholesterol, triglyceride, low-density lipoprotein cholesterol, high-density lipoprotein cholesterol, lactate, non-esterified fatty acid, norepinephrine, epinephrine, plasma renin activity, angiotensin Ⅱ, angiotensin-converting enzyme 2, neuropeptide Y, atrial natriuretic peptide, lactate dehydrogenase, insulin, glucocorticoid, adiponectin, and leptin.

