## Abstract

Cardiorespiratory function influences exercise capacity and is an important determinant of high-altitude adaptation. Some studies have investigated the characteristics of changes in cardiorespiratory fitness during high-altitude acclimatization. However, studies on changes in cardiorespiratory fitness during high-altitude de-acclimatization are still lacking and have not yet been elucidated. Furthermore, few drugs have been studied to improve cardiorespiratory function during both processes. The Shigatse CARdiorespiratory Fitness (SCARF) study is a single-center, randomized, double-blind, placebo-control clinical trial to explore the effects of ubiquinol on cardiorespiratory fitness during high-altitude acclimatization and de-acclimatization in healthy adults. Participants will be randomly assigned 1:1 to ubiquinol 200 mg daily or a placebo for 14 days before departure until the end of data collection after return in 7 days. Cardiorespiratory fitness is the primary outcome, while acute mountain sickness and high-altitude de-acclimatization symptoms are secondary endpoints. In addition, laboratory measurements, including routine blood tests and serological measurements, will be performed. To the best of our knowledge, the SCARF study will be the first to reveal the changes in the cardiorespiratory fitness characteristics during high-altitude acclimatization and de-acclimatization. Furthermore, the results of this study will contribute to exploring whether ubiquinol supplementation could be beneficial for endurance exercise capacity at different altitudes and help improve adaptation to acute hypoxia and de-acclimatization.

**Clinical Trial Registration:** This study has been registered in the Chinese Clinical Trial Register (www.chictr.org.cn) as ChiCTR2200059900 and ChiCTR2200066328.

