### Setting

2.1.

This is a single-center, randomized, double-blind, placebo-control clinical trial conducted at Chongqing Xinqiao Hospital and Shigatse Branch Hospital [The Shigatse CARdiorespiratory Fitness (SCARF) Study] in 2022 and registered at www.chictr.org.cn (ChiCTR2200059900 and ChiCTR2200066328). The primary hypothesis of this study is that ubiquinol supplementation may improve cardiorespiratory fitness both at high-altitude acclimatization and de-acclimatization, while AMS and HADAS are secondary endpoints. The study complies with the SPIRIT 2013 recommendations (Standard Protocol Items: Recommendations for International Trials) (24) (Supplementary Material S1). Table 1 depicts the overall schedule and time commitment for trial participants.

**Table 1 T1:** Study schedule and time commitment.

Timepoint	Study period					
	Enrolment	Allocation	Post-allocation			Close-out
	−14 days	0	11 days	17 days	28 days	6 months
Enrolment						
Eligibility screen	X					
Informed consent	X					
Medical and travel history	X					
Vital signs	X					
Allocation/randomization		X				
Interventions						
Ubiquinol group						
Placebo group						
Assessments						
Baseline variables: age, sex, height, weight			X			
Outcome variables						
CPET			X	X	X	X
Blood routine examination			X	X	X	
Serum marker examination			X	X	X	
The Lake Louise 2018 score assessment				X		
High altitude de-acclimatization syndrome assessment					X	X

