### Recruitment and study population

2.2.

Enrolment occurred in Chongqing (low altitude area, 300 m) from June 1st, 2022, and ended on June 15th, 2022. Demographic and medical data of all participants were recorded through interviews. A potential participant must meet all the inclusion criteria and do not meet any exclusion criteria. The inclusion and exclusion criteria are detailed in Table 2. According to previous studies, the risks associated with CoQ10 are minor, even at doses as high as 1,800 mg (25). Moreover, pharmacokinetic studies suggest that exogenous CoQ10 does not influence the biosynthesis of endogenous CoQ10 and is less likely to accumulate in plasma or tissues after the cessation of supplementation (26).

**Table 2 T2:** Inclusion and exclusion criteria.

Inclusion criteria	Age >18 years
	Chinese Han people
	Have no recent (previous 6 months) experience in resistance exercise (including additional cardiopulmonary exercise tests, long-distance running, riding, swimming and skiing and other endurance exercise)
	Are able to perform leg-based resistance exercise
	Are free from musculoskeletal injury (past 6 months)
	Lived at low altitudes (<500 m) for at least 10 years
	Had no recent exposure to high altitude (>2,500 m) (in the last 6 months)
	Willing and capable of providing written informed consent and complying with the study protocol
Exclusion criteria	Incapable of giving informed consent
	Respiratory and cardiovascular diseases
	Liver and kidney dysfunctions
	Malignant tumors
	Coagulation disorders
	A history of AMS
	History of angioedema
	A history of syncope (hypoglycemia excepted)
	Psychiatric disorders or neuroses
	Ubiquinol supplementation with any side-effect in the first 14 days before departure
	Pregnant or nursing women
	A recent history (previous 1-month period) of drug use with acetaminophen, aspirin, nonsteroidal anti-inflammatory drugs
	A recent history (previous 1-month period) of drug use of acetazolamide, diuretics, or other drugs for the prevention or treatment of AMS
	A recent history (previous 1-month period) use of consuming ergogenic aids (e.g., creatine monohydrate), protein-based supplements, or nutritional supplements that may alleviate muscle damage (e.g., antioxidants, polyphenols)
	Other diseases that prevent the patient from going to high altitudes
	Involuntary participant status

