### Sample size

2.3.

The G-power tool (version 3.1.9.2, Germany, 2017) was used to calculate the sample size by prior power analysis and to estimate all statistically significant results. The *α* error probability was set at 0.05, and the power (1 − *β*) was set at 0.9. With a correlation among repeated measures of 0.5, a sample size of 39 was determined to be necessary to assess the effects of ubiquinol. A sample size of 36 within two groups (ubiquinol group and placebo group) and within-between interactions were calculated with a nonsphericity correction (*ε*) of 1. Considering a 5% dropout rate, based on a sample size of 39, 41 participants would be required finally.

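### Travel to altitude is conditional on having no side-effects during 14 days of randomized treatment, so the altitude and post-return comparisons are not fully protected by randomization

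*Protocol article*

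**What the plan says.** The Abstract gives the order of events: "Participants will be randomly assigned 1:1 to ubiquinol 200 mg daily or a placebo for 14 days before departure". Table 1 (section 2.1) puts allocation at day 0 and the post-allocation assessments at days 11, 17 and 28.

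Section 2.6 (Study design) makes travel conditional on tolerating that 14-day period: "only participants who did not experience these adverse effects would go to the high altitude as scheduled". Its reason is: "It would help us identify related symptoms at high altitudes due to hypoxia rather than adverse events of ubiquinol". Table 2 (section 2.2) lists among the exclusion criteria: "Ubiquinol supplementation with any side-effect in the first 14 days before departure".

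The primary hypothesis (section 2.1) is that "ubiquinol supplementation may improve cardiorespiratory fitness both at high-altitude acclimatization and de-acclimatization", so it needs measurements made at altitude and after return. Section 2.3 allows for losses as follows: "Considering a 5% dropout rate, based on a sample size of 39, 41 participants would be required finally". The article gives no side-effect rate; section 2.2 calls the risks of CoQ10 minor.

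**The concern.** An eligibility criterion should be settled before allocation. This one cannot be, because it depends on what happens during 14 days of assigned treatment and that treatment can bring it about. Randomization makes the arms comparable at day 0. It does not make comparable the two subsets left after a filter that may act differently in each arm.

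The outcomes behind the primary and secondary endpoints exist only for people who pass the filter. The filter also overlaps with the secondary endpoints, because several adverse events in Table 3 are also items scored for AMS or HADAS. People prone to such complaints may be removed before those scores are taken, possibly in different numbers by arm.

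The trial is small, so a few removals matter for precision as well as for comparability.

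**Working it through.** **Timing.** Allocation is at day 0. Treatment runs for 14 days, with tests on the last three of them. The altitude programme falls on the third day after arrival (day 17). Return follows 7 days at altitude, and the last programme of this phase is on the 7th day after return (14 + 7 + 7 = day 28). The side-effect window is days 0 to 14, wholly after allocation.

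**Overlap of trigger and outcome.** Table 3 includes upset stomach, nausea, diarrhea, loss of appetite, palpitation, insomnia and dizziness. In section 2.8, gastrointestinal symptoms and dizziness count towards the Lake Louise score. Dizziness, insomnia, palpitation, reduced appetite and diarrhea are HADAS items.

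**The two passages side by side.** Table 2 words the criterion as a side-effect of ubiquinol. Read literally, that needs knowledge of the allocation. Section 2.6 applies to participants generally, and the preceding sentence refers to reactions to exercise as well as to ubiquinol. The scope of the rule therefore differs between the two.

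**The plan's own figure.** 39 / (1 − 0.05) = 41.05 and 39 × 1.05 = 40.95, so the stated 41 reproduces to the nearest integer. The allowance is 41 − 39 = 2 participants, for all causes together.

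**Losses from the rule alone.** The side-effect rates are assumptions, since the article gives none. With a 21/20 split, expected loss = 21 × p_u + 20 × p_p, where p_u and p_p are the rates on ubiquinol and placebo. The chance of three or more losses is binomial within each arm. The N needed to keep 39 is 39 / (1 − average rate), rounded up.

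| Ubiquinol / placebo | Expected loss of 41 | Share | P(3 or more lost) | N to keep 39 |
|---|---|---|---|---|
| 2% / 2% | 0.42 + 0.40 = 0.82 | 2.0% | 0.05 | 40 |
| 5% / 0% | 1.05 + 0 = 1.05 | 2.6% | 0.09 | 40 |
| 5% / 5% | 1.05 + 1.00 = 2.05 | 5.0% | 0.34 | 42 |
| 10% / 5% | 2.10 + 1.00 = 3.10 | 7.6% | 0.61 | 43 |
| 20% / 10% | 4.20 + 2.00 = 6.20 | 15.1% | 0.96 | 46 |

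Break-even is an average rate of 5% over both arms. With no events on placebo, that means 2.05 / 21 = 9.8% on ubiquinol.

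If the 5% is meant only for ordinary dropout, and side-effects occur on ubiquinol alone, total loss = 1 − 0.95 × (1 − p_u / 2). This gives 7.4%, 9.8% and 14.5% for p_u of 5%, 10% and 20%, and N of 43, 44 and 46.

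**Possible bias.** Suppose those removed average s SD below their whole arm on a fitness measure. The mean of those remaining then rises by s × p / (1 − p). The difference between arms is s × [p_u / (1 − p_u) − p_p / (1 − p_p)].

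- Equal rates: 0, provided s is the same in both arms.
- 10%/5%: s × (0.1111 − 0.0526) = 0.0585 s, or 0.03 to 0.06 SD for s from 0.5 to 1.
- 20%/10%: s × (0.2500 − 0.1111) = 0.1389 s, or 0.07 to 0.14 SD.

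The value of s is also an assumption. The sign reverses if those removed are fitter than average, or if the placebo rate is the higher one.

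**The case against.** The strongest objection is that the harm is conjectural. The risks are described as minor, and at 2%/2% or 5%/0% the expected loss is about one person, inside the allowance. Section 2.3 also gives 36 for the within-between interaction; at 10%/5% about 38 remain, which is above 36. A stable fitness difference would largely cancel from the treatment-by-altitude interaction if the same people contribute their low-altitude test. A screen of this kind can reduce drug-related symptoms at altitude. Adverse events are collected throughout and are safety endpoints, so nothing says that pre-departure events are discarded. Analysis sets and missing-data methods may be in a plan that is not shown.

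Much of this stands, and it limits the point. A reader might infer that the rule exceeds the 5% allowance, that its losses lie outside that allowance, or that the bias favours ubiquinol. The documents support none of these. They give no rate, do not say what the 5% covers, and do not show who would be removed.

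The objection does not remove the rule itself, which is stated rather than left to another document. Its stated purpose is already served by the placebo arm. The Abstract has dosing continue until the end of data collection after return, so drug effects can still arise at altitude. The cancellation argument does not cover AMS and HADAS, or the between-group comparisons at each altitude planned in section 2.11.2. The unweighted GEE named there can allow for missingness that depends on treatment alone. It cannot allow for missingness that depends on symptoms related to the outcome and absent from the model.

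**Conclusion.** The concern holds in a limited form. The plan applies a treatment-dependent exclusion after randomization and labels it an eligibility criterion. The day-17, day-28, AMS and HADAS comparisons are therefore not fully protected by randomization. This rests on the stated timing and wording alone.

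The size of the problem is not determined. Bias is near zero if side-effect rates are low and equal. It runs towards ubiquinol if ubiquinol causes more side-effects and those removed are less fit or more symptom-prone; in the illustrations with unequal rates it is 0.03 to 0.14 SD. On sample size, all that can be said is that two losses from any cause use up the allowance, that section 2.3 does not say whether these exclusions are included, and that they pass 5% in expectation only if the average rate over both arms is above 5%.

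**What to change.** 1. Stop treating the Table 2 item as an eligibility exclusion and record it as a post-randomization event.
2. Reconcile Table 2 and section 2.6 with each other and with the time of randomization, as one rule applied blind and identically in both arms. Which events preclude travel is not for this review to set.
3. Analyse all randomized participants in their allocated arm. Use any pre-departure CPET they have and all their adverse events. Those who stopped before the tests at days 11 to 14 may have no CPET, and those tests are themselves made on treatment.
4. Report the number not travelling, with reason, by arm.
5. Add a sensitivity analysis, for example a tipping point, for their missing day-17 and day-28 values.
6. State whether the 5% includes these exclusions and what side-effect rate was assumed.
7. Limit the conclusions according to how many did not travel and how they split by arm.

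The cost is wording in Table 2 and sections 2.3, 2.6 and 2.11.2, plus one extra analysis, all of which can be settled before allocation is revealed. The downside is that missing altitude data must be modelled. Enrolment ended in June 2022, so rewording cannot restore altitude outcomes for anyone already kept from travelling.

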**Figure 1 F1:**
[figure not shown]
The flow chart of this study.

### Laboratory tests

2.7.

Participants will be requested to avoid eating or drinking anything apart from water for up to 12 h. Participants' blood samples will be collected between 8:00 and 8:15 am the day before the exercise tests at different altitudes using the same procedure. After sitting quietly for 15 min, approximately 5 ml of intravenous blood of participants will be collected from the vein at the cubital fossa in the elbow with a tourniquet and mixed immediately with 1 ml of the anticoagulant, dipotassium ethylenediaminetetraacetic acid. Blood samples will be divided into 1 ml and 4 ml parts. The first 1 ml will be analyzed using a BC-3000 plus automated hematology corpuscle analyzer (Shenzhen, China), and the 4 ml will be subjected to high sensitivity enzyme-linked immunosorbent assay kit (Jiangsu Jingmei Biological Technology Co., Ltd., China) for the 19 kinds of circulating parameters. Blood collected at high altitude will be frozen in a −20°C transfer tank and flown to Xinqiao Hospital within 3 h. All blood samples will be measured for biochemical parameters at the Clinical Laboratory of Cardiology Science of Xinqiao Hospital.

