## Discussion

3.

To the best of our knowledge, this study is the first to evaluate cardiorespiratory fitness prospectively and accurately during the high-altitude acclimatization and de-acclimatization process. Moreover, it is a double-blinded, placebo-controlled trial to explore the effects of ubiquinol on cardiorespiratory fitness during acclimatization and de-acclimatization. The clinical trial design depicts cardiorespiratory fitness characteristics at high-altitude acclimatization and de-acclimatization and is designed to reveal cardiovascular and respiratory function restoration during de-acclimatization. In addition, we determine whether ubiquinol supplementation is beneficial for endurance exercise capacity at a high altitude and helps with better adaptation to acute hypoxia exposure. Furthermore, we explore the relationship between the circulating substances and physical performance capacity at high altitudes to be able to account for the possible mechanisms.

The exploration of medicines for high-altitude acclimatization has been underway for decades. A few drugs, such as acetazolamide and *Rhodiola rosea*, have been recommended to promote acclimatization (16, 44, 45). However, limited research focused on the process of de-acclimatization and related symptoms. Thus, in this study, we recruited healthy Han Chinese from Chongqing to assess the possible effect of ubiquinol on cardiorespiratory fitness, AMS, and HADAS symptoms. A previous trial has reported that CoQ10 supplementation with a dose of 90 mg for 6 weeks orally could improve VO_2_max, aerobic, and anaerobic thresholds, indicating the increase of cardiorespiratory fitness of endurance athletes (21). In addition, studies demonstrated that CoQ10 deficiency was positively associated with fatigue, whereas serum CoQ10 levels were inversely correlated with fatigue severity (46, 47). In addition, another meta-regression also confirmed that a daily dose of CoQ10 was associated with fatigue reduction (48). Therefore, we suppose that ubiquinol supplementation at high altitudes may alleviate AMS and HADAS-related symptoms and maintain cardiorespiratory fitness.

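### Glucose and lactate are assigned to a K2EDTA sample with no glycolysis inhibitor named, so both drift in the tube by an amount set by an unstated delay that may differ by altitude (minor)

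*Protocol article*

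**What the plan says.** The Laboratory tests section (2.7) describes one draw of about 5 ml, "mixed immediately with 1 ml of the anticoagulant, dipotassium ethylenediaminetetraacetic acid". Only after mixing is the blood divided. A 1 ml part goes to the haematology analyser, and "the 4 ml will be subjected to high sensitivity enzyme-linked immunosorbent assay kit" for the 19 circulating parameters. No other additive, tube or portion is named.

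The Study design section (2.6) lists those analytes: "a serological test of 19 circulating indicators, including glucose, total cholesterol, triglyceride" and, further on, "high-density lipoprotein cholesterol, lactate, non-esterified fatty acid". Glucose and lactate are therefore assigned to the EDTA-treated portion.

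On handling after the draw, section 2.7 says: "Blood collected at high altitude will be frozen in a −20°C transfer tank and flown to Xinqiao Hospital within 3 h". It adds: "All blood samples will be measured for biochemical parameters at the Clinical Laboratory of Cardiology Science of Xinqiao Hospital". It gives no time from draw to separation or freezing for either site, and no handling step for low-altitude blood. The draw itself is standardised: same clock window and same procedure at each altitude.

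On use, the Discussion says "we explore the relationship between the circulating substances and physical performance capacity at high altitudes" to help account for possible mechanisms. Section 2.5 lists neither analyte as a primary or secondary outcome.

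**The concern.** Blood cells go on consuming glucose and releasing lactate after the draw, and an anticoagulant alone does not stop them. A measured value is then the participant's value plus a processing term that grows with time and with cell count. The article does not merely leave tube type unmentioned; it fixes one, and that choice does not suit two of the listed analytes.

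The altitude comparison is the exposed one. Altitude is a model term, and the two sites' samples follow different paths: only Shigatse blood is described as frozen and flown. If the time to separation or freezing differs between sites, the processing term is confounded with altitude. Cell count may also change with altitude (an assumption here), which would alter the drift even at equal delays. Later storage cannot undo drift that has already happened. What is at stake is a handling artefact being read as metabolic adaptation.

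**Working it through.** **Figures in the plan.** There is none to reproduce. The article states no glucose or lactate level, SD, expected effect, glycolysis rate or delay. The calculation below is a sensitivity range on assumed inputs.

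**Assumed inputs.** Starting glucose G0 = 5 mmol/L; fractional loss r = 2–10% per hour in unseparated, unfrozen blood; delay t = 0.25–3 h.

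**Formulas.** Glucose fall = G0 × (1 − (1 − r)^t). Lactate rise ≤ 2 × glucose fall, since one mole of glucose gives at most two of lactate.

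**Results** (glucose fall / ceiling on lactate rise, mmol/L):

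| r per hour | 15 min | 1 h | 3 h |
|---|---|---|---|
| 2% | 0.03 / 0.05 | 0.10 / 0.20 | 0.29 / 0.59 |
| 5% | 0.06 / 0.13 | 0.25 / 0.50 | 0.71 / 1.43 |
| 7% | 0.09 / 0.18 | 0.35 / 0.70 | 0.98 / 1.96 |
| 10% | 0.13 / 0.26 | 0.50 / 1.00 | 1.355 / 2.71 |

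Example: at 10% and 3 h, 5 × (1 − 0.9³) = 5 × 0.271 = 1.355, and 2 × 1.355 = 2.71.

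The lactate figures are ceilings. If only a share of 0.55 appears as a plasma rise (a further assumption), the rise at 1 h for r = 5–7% is 2 × 0.25 × 0.55 = 0.28 to 2 × 0.35 × 0.55 = 0.39 mmol/L, instead of 0.50–0.70.

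**Relative size.** For glucose the fall runs from 0.5% (2% per hour, 15 min) to 27% (10% per hour, 3 h). Against an assumed resting lactate of 1 mmol/L, the ceiling is 5–26% at 15 min and 59–271% at 3 h. Lactate is the more fragile of the two.

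**What reaches each contrast.**
- *Altitude.* The bias is the difference in drift between sites. For illustration, take r = 5% with 15 min at one site and 1 h at the other. The spurious glucose difference is 0.25 − 0.06 = 0.19 mmol/L, and the lactate difference is at most 0.50 − 0.13 = 0.37 mmol/L. With equal delays and equal cell counts it is zero.
- *Arm.* Both arms share the handling at each altitude, and laboratory staff are blinded (section 2.4.1). Drift common to both arms cancels, to a first approximation, from the within-altitude arm difference and from the treatment-by-altitude term. Variation in delay between samples remains as noise.
- *Correlations with exercise-test variables.* Within an altitude they are weakened by noise. Pooled over altitudes they could also carry any site difference.

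**The case against.** The strongest objection is that tube choice matters only through the delay, and a condensed article may leave separation steps and time limits to the full protocol. With prompt separation or freezing the drift is negligible: 0.03–0.06 mmol/L of glucose at 15 min for 2–5% per hour. This stands as a limit on size. It does not remove the point, because the additive and the split of the sample are stated and would make the result depend on that delay. It does mean that one can say only that no glycolysis inhibitor is named, not that none was used.

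Four stronger readings are tempting, and the documents support none of them:
- *That the drift is as large as the altitude or treatment effects sought.* No expected effect, SD or delay is given, so there is nothing to compare it with.
- *That blood stands unfrozen for 3 hours.* The only 3 h in section 2.7 is the transport of blood already frozen. Low-altitude blood is measured at a study hospital in Chongqing, so no long journey is implied there either.
- *That the randomised comparison is biased.* Shared handling and blinded laboratory staff make this unlikely; the cost is precision.
- *That the trial's mechanistic case falls.* The rationale in the Introduction concerns the anaerobic threshold and anaerobic production under load, which the exercise test addresses through VO2 at the anaerobic threshold. The blood is fasting, resting and taken the day before exercise, so a better tube would not give lactate under load. Glucose and lactate are 2 of 19 exploratory markers.

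**Conclusion.** The point holds in limited form, and its severity is minor. The plan assigns glucose and lactate to K2EDTA blood with no glycolysis inhibitor named. The direction of drift is certain: glucose down, lactate up. Its size is not known. On the assumed 2–10% loss per hour from 5 mmol/L, it runs from trivial at a few minutes to material at 1–3 h. The altitude contrast for these two analytes is biased only if delay or cell count differs by site. The documents make a difference in delay possible, by describing a separate path for high-altitude blood, but do not show one. The arm contrast mainly loses precision, and the primary outcome (cardiorespiratory fitness) and secondary outcomes (AMS and HADAS) are untouched.

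**What to change.** **If samples remain to be drawn.** Take glucose and lactate into a small glycolysis-inhibiting (fluoride) tube from the same venepuncture, and separate within one fixed time at both sites. Keep K2EDTA for the blood count and the other uses. The cost is one extra small tube, a line in section 2.7 and a check that the assay kit accepts that tube.

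**If sampling is complete.** This is likely: enrolment closed on 15 June 2022, the Study design section singles out the six-month visit as still to come, and Table 1 schedules no blood or serum tests then. Report the time from draw to separation or freezing by site. Where those times are known and equal, present the results with a note on the tube. Where they are unknown or unequal, do not interpret glucose or lactate across altitudes. This costs a short table and one sentence of limitation.
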